#### Step 2: Anemia Correction in Adjuvant (Chemo)radiation Therapy

Anemia will be corrected after performing blood tests on the day of computed tomography (CT) simulation, during (concurrent chemo-) radiation therapy ((CC)RT), and every 3 weeks (visit window±1 week) after the end of treatment. The hemoglobin level will be re-evaluated at 3 weeks after the end of treatment. The treatment and examination schedule for step 2 is shown in Figure 3.

**Figure 3 F3:**
[figure not shown]
Examination and treatment of anemia in step 2 (radiation therapy). CT, computed tomography; Hb, hemoglobin; PBM, patient blood management; RT, radiation therapy; wks, weeks.

##### Patient Blood Management Group

If the hemoglobin level is between 7 g/dL and 12 g/dL in the pre-treatment blood test, 1000 mg of ferric carboxy-maltose will be administered; if the hemoglobin level is 7 g/dL or less, two packs of RBC will be transfused.

##### Conventional Management Group

If the hemoglobin level is between 8 g/dL and 10 g/dL, one pack of RBC will be transfused; if the hemoglobin level is 8 g/dL or less, two packs of RBC will be transfused. Erythropoietin and oral iron supplements will be allowed but not intravenous iron supplements.

#### Step 3: Anemia Correction in Adjuvant Chemotherapy

Anemia will be assessed by performing blood tests the day before the start of chemotherapy and every two cycles during chemotherapy. The hemoglobin level will be re-evaluated at 3 weeks after the end of treatment. The treatment and examination schedule for step 3 is shown in Figure 4.

**Figure 4 F4:**
[figure not shown]
Examination and treatment of anemia in step 3 (chemotherapy). Chemo, chemotherapy; Hb, hemoglobin; PBM, patient blood management; wks, weeks.

##### Patient Blood Management Group

If the hemoglobin level is between 8 g/dL and 12 g/dL in the pre-treatment blood test, 1000 mg of ferric carboxy-maltose will be administered; if the hemoglobin level is 8 g/dL or less, two packs of RBC will be transfused. Erythropoietin may be used in patients with a symptomatic hemoglobin level of 12 g/dL or less or an asymptomatic hemoglobin level of 8 g/dL or less.

##### Conventional Management Group

If the hemoglobin level is between 8 g/dL and 10 g/dL, one pack of RBC will be transfused; if the hemoglobin level is 8 g/dL or less, two packs of RBC will be transfused. Erythropoietin and oral iron supplements will be allowed but not intravenous iron supplements.

### Participants

#### Inclusion Criteria

Study patients must satisfy all of the following selection criteria: (1) women aged 20–80 years; (2) untreated histologically diagnosed cervical cancer, endometrial cancer, or ovarian cancer (including cases diagnosed by imaging without biopsy in the case of ovarian cancer); (3) Eastern Cooperative Oncology Group performance status 0–2; (4) American Society of Anesthesiologists physical status 1 or 2; (5) pre-operative hemoglobin ≥7 g/dL; (6) scheduled to undergo pre-operative iron panel test (serum ferritin, iron, total iron binding capacity, transferrin); (7) proper organ function with white blood cell count >3000/μL, platelet >100 000/μL, creatinine <2.0 mg/dL, bilirubin <1.5× normal, and serum glutamic-pyruvic transaminase, serum glutamic-oxaloacetic transaminase, and alkaline phosphatase ≤3× institutional upper limit normal; and (8) voluntarily signed the informed consent form.

#### Exclusion Criteria

The exclusion criteria are as follows: (1) unable to provide informed consent on their own; (2) allergic to existing iron preparations; (3) underwent neoadjuvant chemotherapy or pre-operative radiation therapy; (4) have had or received cancer treatment within 5 years, except for non-melanoma skin cancer, cervical intra-epithelial tumor, and superficial cancer of the stomach and bladder; (4) presence of iron overload or iron utilization disorders; and (5) serum ferritin >800 ng/mL or transferrin saturation >50% on iron panel tests.

### Endpoints

The primary endpoint is the rate of transfusion within 3 weeks after surgery. The secondary endpoints include transfusion rate within 3 weeks after radiation and chemotherapy, and the comparison of hemoglobin levels, frequency of anemia and blood transfusion before adjuvant therapy, frequency of delayed adjuvant therapy due to anemia, cost-effectiveness, quality of life, and adverse events after iron supplement treatment or blood transfusion.

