**Primary Endpoint:**

Rate of transfusion within 3 weeks after surgery.

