##### Conventional Management Group

If the hemoglobin level is between 8 g/dL and 10 g/dL, one pack of RBC will be transfused and, if the hemoglobin level is 8 g/dL or less, two packs of RBC will be transfused. Erythropoietin and oral iron supplements will be allowed, but not intravenous iron supplements. During surgery, the need for transfusion will be decided according to the judgment of the operating surgeon and anesthesiologist in case of hemodynamic instability. A blood test will be performed the day after surgery, and if the hemoglobin level is between 8 g/dL and 10 g/dL, one pack of RBC will be transfused; if the hemoglobin level is 8 g/dL or less, two packs of RBC will be transfused. Post-operatively, erythropoietin and oral iron supplements will be allowed. The hemoglobin level will be re-evaluated 3 weeks post-operatively.

Surgical treatment and adjuvant treatment will be carried out according to the guidelines published by the Korean Society of Gynecological Oncology, which are consistent with the recent guidelines of the National Comprehensive Cancer Network. All surgery-related complications occurring during and after surgery during hospitalization will be evaluated using Dindo’s classification.^14^

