### Sample Size

We performed sample size calculation through the Z-test with unpooled variance. Previous studies showed that the expected transfusion rate without patient blood management is 40%,^15 16^ and that the blood transfusion rate could be reduced by 25% through patient blood management. The following assumptions were made for calculating the required number of study participants: transfusion rate before, during, and after surgery when implementing patient blood management of 40%; level of significance α=0.05 (two-sided); and type II error, β=0.2 (ie, power=80%). The sample size was calculated using PASS version 15 (NCSS, Kaysville, Utah, USA) using the above settings and a total of 150 patients per group (total of 300 patients) were deemed necessary. Considering a dropout rate of 10%, we intend to enroll 167 patients per group (total 334 patients).

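### The primary endpoint is worded as transfusion in the 3 weeks after surgery, but the planning rate covers before, during and after surgery; the window's opening must be stated and the two aligned

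*Protocol article*

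**What the plan says.** **Endpoint.** The Endpoints section of the protocol article states: "The primary endpoint is the rate of transfusion within 3 weeks after surgery". The abstract has the same wording: "Rate of transfusion within 3 weeks after surgery". Neither says when the window opens.

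**Planning rate.** The Sample Size section says that "the expected transfusion rate without patient blood management is 40" percent and that "the blood transfusion rate could be reduced by 25% through patient blood management". Its list of assumptions then gives a "transfusion rate before, during, and after surgery when implementing patient blood management of 40" percent. That second sentence is the only one that attaches a period to the rate, and it assigns the 40% to the wrong arm.

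**What happens before surgery.** Step 1 places the first blood test and correction of anemia 2 to 6 weeks before the operation, in both groups.
- Conventional Management Group: a red-cell transfusion is mandated at any hemoglobin up to 10 g/dL, one pack in the 8 to 10 g/dL band and two packs below it. The intra-operative and day-after-surgery rules follow separately, so this first rule is pre-operative.
- Patient Blood Management Group: intravenous iron for hemoglobin of 7 to 12 g/dL, with no pre-operative transfusion rule. The inclusion criteria require hemoglobin of at least 7 g/dL.

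**The concern.** The article describes the counted period in two ways. If the endpoint wording is followed as written, a class of transfusions that the protocol itself creates, in one arm only, is not counted. The loss can also carry forward: an uncounted transfusion before surgery raises hemoglobin and makes a counted one under the day-after-surgery rule less likely.

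Pre-operative correction of anemia is part of what step 1 is meant to evaluate, since the trial design describes step 1 as covering the time before, during and after surgery. A window that opens at surgery gives the blood management program no credit for transfusions avoided before it.

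Because the trial is unblinded, an open question about which transfusions count could be settled after transfusions by arm are known.

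**Working it through.** **Inputs from the Sample Size section:** control rate 0.40; two-sided α = 0.05 (z = 1.960); power 80% (z = 0.842); unpooled Z-test; 10% dropout. Allocation is 1:1 (Randomization and Blinding).

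**Step 1. Reproduce the plan's figure.**

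n per group = (p₁q₁ + p₂q₂)(1.960 + 0.842)² / (p₁ − p₂)²

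With 0.40 against 0.25: (0.2400 + 0.1875) × 7.849 / 0.0225 = 149.1, so 150. With dropout, 150 / 0.9 = 166.7, so 167. Both match the article.

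Other readings of the 40% and the 25% do not give 150:

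| Rates compared | n per group |
|---|---|
| 40% vs 30% | 354 |
| 40% vs 15% | 47 |
| 65% vs 40% | 59 |
| 55% vs 40% | 171 |
| 53.3% vs 40% | 216 |

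Of the readings tried, only 40% control against 25% blood management works. The 40% is therefore the control rate in the calculation, and the sentence that labels it as the rate with blood management is mislabelled. The arithmetic itself is sound.

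**Step 2. Compare the periods.**

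| Transfusions | Planning rate as worded | Endpoint read literally | Protocol rule |
|---|---|---|---|
| Pre-operative | counted | not counted | mandated in the conventional arm only |
| Intra-operative | counted | unclear | clinical judgment, both arms |
| Post-operative to 3 weeks | counted | counted | both arms, different hemoglobin triggers |

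**Step 3. Illustrate the size.** Let x be the share of control patients transfused only before surgery. The article does not give x, so the values below are assumptions. The blood management rate is held at 25%.

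Power = Φ(|p₁ − p₂| / √[(p₁q₁ + p₂q₂)/150] − 1.960)

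- x = 0: SE = √(0.4275/150) = 0.0534; 0.15/0.0534 = 2.81; power 80.2%.
- x = 5 points: SE = √(0.4150/150) = 0.0526; 0.10/0.0526 = 1.90; power about 48%.

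| x (points) | Counted rates | Power at 150 per arm |
|---|---|---|
| 0 | 40% vs 25% | 80% |
| 2 | 38% vs 25% | 69% |
| 3 | 37% vs 25% | 62% |
| 5 | 35% vs 25% | 48% |
| 10 | 30% vs 25% | 16% |

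**Step 4. Check that one-sidedness drives the loss.** If 5 points were lost from both arms (35% vs 20%), SE = √(0.3875/150) = 0.0508 and power would be about 84%. Power falls in step 3 because the events are removed from one arm only.

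**The case against.** **The phrase may mark only the close of the window.** The Endpoints section uses the same form for transfusion after radiation and chemotherapy. In steps 2 and 3, testing and transfusion take place before and during treatment, and hemoglobin is re-evaluated 3 weeks after its end. A window opening only at the end of treatment would miss most of what those steps manage. On this reading endpoint and planning rate agree. This is a fair reading, and it means the text does not show that pre-operative transfusions are excluded. It does not remove the need to say so in an unblinded trial.

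**The period of the control rate is not firmly established.** The sentence giving 40% for controls names no period, and the one that names a period mislabels the arm. This stands: the period over which the 40% was observed cannot be settled from the article. It is a further reason to restate the basis of the rate.

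**A reader might infer that the trial is underpowered.** The documents do not support that. The pre-operative-only share is unknown. A loss of 10 points would need a quarter of the transfused controls (10 of 40) to be transfused before surgery and never again. A control patient at 10 g/dL or less the day after surgery must be transfused then, so many of those transfused earlier would still count.

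**A reader might also infer that the observed difference must shrink overall.** That does not follow either. The post-operative transfusion triggers differ (10 g/dL conventional, 7 g/dL blood management) and push the difference the other way. What holds is the relative statement: for the same patients and rules, dropping control-only events gives a smaller contrast than counting them.

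**A post-operative window could be chosen on purpose.** It depends less on the assigned pre-operative rules and, if anything, works against the new program. That is defensible, but the planning rates would then have to refer to that window.

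**Conclusion.** The mismatch is real and lies within the article: Endpoints and abstract name one period, Sample Size another. The literal endpoint omits pre-operative transfusions, which the protocol mandates only in the conventional arm, and leaves intra-operative ones unclear in both arms. Whether that omission is intended cannot be determined from the text.

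The consequence is a smaller contrast than an endpoint covering the planned period would give. Its size cannot be fixed from the documents. The fall in power from 80% to between 69% and 16% rests on assumed losses of 2 to 10 points, a blood management rate held at 25%, no change in intra-operative counting, and 150 evaluable patients per arm. It shows sensitivity and is not a forecast.

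This is an ambiguity in the primary endpoint that should be resolved before transfusion results are compared by arm. It does not show that the sample size is wrong.

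**What to change.** Define the primary endpoint as the proportion of randomised patients with any red-cell transfusion from randomisation to 3 weeks after surgery, counting pre-, intra- and post-operative transfusions. Report the three periods separately as components. Use the same wording in the abstract, Endpoints and Sample Size, and correct the assumption sentence so that the 40% is attached to the conventional arm.

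If a window restricted to the time after surgery is intended, say so, state whether intra-operative transfusions count, and restate both planning rates and the power for that window.

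The cost of the first route is an amendment to the endpoint wording. The sample size stays at 150 per group (167 with dropout), and no treatment rule changes. Under the second route the sample size may need to change, depending on the restated rates.

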### Sample Size

We performed sample size calculation through the Z-test with unpooled variance. Previous studies showed that the expected transfusion rate without patient blood management is 40%,^15 16^ and that the blood transfusion rate could be reduced by 25% through patient blood management. The following assumptions were made for calculating the required number of study participants: transfusion rate before, during, and after surgery when implementing patient blood management of 40%; level of significance α=0.05 (two-sided); and type II error, β=0.2 (ie, power=80%). The sample size was calculated using PASS version 15 (NCSS, Kaysville, Utah, USA) using the above settings and a total of 150 patients per group (total of 300 patients) were deemed necessary. Considering a dropout rate of 10%, we intend to enroll 167 patients per group (total 334 patients).

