**Study Hypothesis:**

Patient blood management will reduce the transfusion rate by up to 25%.

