### Randomization and Blinding

Patients will be randomly assigned in a 1:1 ratio to the patient blood management group and the conventional management group. A randomization table will be prepared using SAS software (SAS Institute, Cary, North Carolina, USA) by an independent statistician and study patients will be assigned using the stratified block randomization method. Stratification will be performed according to the type of cancer, International Federation of Gynecology and Obstetrics stage, and methods of surgery. Due to the nature of the study, blinding is not possible.

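### The sample-size text misstates the effect and the arm: 150 per group fits 40% versus 25%, not a rate reduced by 25% and not 40% under patient blood management

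*Protocol article*

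**What the plan says.** The method is given in the Sample Size section of the protocol article: "We performed sample size calculation through the Z-test with unpooled variance", with "level of significance α=0.05 (two-sided") and "type II error, β=0.2 (ie, power=80"%). Allocation is 1:1 (Randomization and Blinding).

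Three statements concern the rates:

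- Control rate (Sample Size): "the expected transfusion rate without patient blood management is 40"%.
- Effect (Sample Size): "the blood transfusion rate could be reduced by 25% through patient blood management". The abstract's Study Hypothesis puts it as "Patient blood management will reduce the transfusion rate by up to 25"%.
- Assumption listed for the calculation (Sample Size): "transfusion rate before, during, and after surgery when implementing patient blood management of 40"%.

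The section reports that PASS, run on these settings, gave 150 per group (300 in total), raised to 167 per group (334) for 10% dropout. A transfusion rate of 25% is not stated for either arm.

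**The concern.** There are two separate faults. First, 40% is given to both arms: it is the rate without PBM in one sentence and the rate with PBM in the next. Taken literally, the difference is zero and no finite sample size exists. Second, the 25% is worded as the size of a reduction, and a reduction by 25% from 40%, whether relative or in percentage points, does not lead to 150 per group.

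These sentences are the article's only statement of the effect on the primary endpoint, and the claim of 80% power depends on them. If the hypothesis is read as a 25% relative reduction, the trial would miss that effect more often than it found it. A non-significant result could then be taken as evidence against an effect the trial was not sized to detect.

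**Working it through.** **Inputs.** Unpooled Z-test, two-sided α = 0.05 (z = 1.95996), power 80% (z = 0.84162), 1:1 allocation, dropout 10%. All are stated in the article.

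**Formula, per group.**

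n = (1.95996 + 0.84162)² × [p₁(1−p₁) + p₂(1−p₂)] / (p₁−p₂)², where (2.80158)² = 7.849.

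**The stated figure.** Take 40% for control and 25% for PBM:

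- n = 7.849 × (0.2400 + 0.1875) / 0.15² = 7.849 × 19.0 = 149.1, so **150**.
- Dropout: 150 / 0.9 = 166.7, so **167** per group and 334 in total.

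Both stated figures are matched exactly. In the other direction, solving for the lower rate that gives n = 150 against 40% returns 25.04%.

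**The rates as worded.**

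| Reading | Control | PBM | Calculation | n per group |
|---|---|---|---|---|
| Reduced by 25%, relative | 40% | 30% | 7.849 × 0.4500 / 0.10² = 353.2 | 354 |
| Reduced by 25 points | 40% | 15% | 7.849 × 0.3675 / 0.25² = 46.2 | 47 |
| 40% is the PBM rate, 25% relative | 53.3% | 40% | 7.849 × 0.4889 / 0.1333² = 215.8 | 216 |
| 40% is the PBM rate, 25 points | 65% | 40% | 7.849 × 0.4675 / 0.25² = 58.7 | 59 |
| 40% in both arms, literally | 40% | 40% | difference is zero | none |

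Changing the test does not rescue the two readings with a 40% control rate. For 40% versus 30%, a pooled variance gives 356, a continuity correction 376, and one-sided variants 279 to 300. For 40% versus 15%, the pooled and continuity-corrected figures are 49 and 57.

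**Power at the stated size.** Power = Φ(|p₁−p₂| / SE − 1.95996), with SE = √{[p₁(1−p₁) + p₂(1−p₂)] / n}.

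- 40% vs 25%, n = 150: SE = √(0.4275/150) = 0.0534; Φ(2.810 − 1.960) = **80.2%** (exact binomial 80.3%).
- 40% vs 30%, n = 150: SE = √(0.45/150) = 0.0548; Φ(1.826 − 1.960) = **44.7%** (exact binomial 44.8%).
- 40% vs 15%, n = 150: SE = √(0.3675/150) = 0.0495; Φ(5.051 − 1.960) = **99.9%**.
- 40% vs 30%, n = 167 (no dropout at all): SE = √(0.45/167) = 0.0519; Φ(1.926 − 1.960) = **48.7%**.

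**The case against.** The strongest reply is that this is a slip of language: *by* written for *to*, and an arm label swapped or a negative dropped. On that view 150, 167 and the 80% power are all correct and nothing in the design changes. That is the likeliest explanation, and it limits the size of the correction. It does not make the text right, because the misworded sentences are the hypothesis and the effect assumption themselves. Nor is this a matter of a journal article being brief: the article lists its settings, and those settings do not give its result.

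A second reply is that 40% versus 25% is not the only pair giving 150. If 40% really is the PBM rate, a control rate of 56% also works: 7.849 × (0.2464 + 0.2400) / 0.16² = 149.1. The Introduction cites transfusion rates of 41% to 77%, a range that includes 56%. The arithmetic is correct, but this reading contradicts the 40% control rate in the Sample Size section and makes no use of the 25%. Pairing 40% with 25% remains the only reading that uses both printed figures and returns 150.

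A third reply is that the intended rates are inferred, and the sources cited for them cannot be checked from the article. This is fair as far as it goes. It calls for the sponsor to confirm the rates against the software input before changing the text.

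Finally, the article does not say whether the 25% is relative or absolute. That is so, but neither reading gives 150.

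**Conclusion.** The concern holds. The Sample Size section contradicts itself on which arm has the 40% rate, and a reduction by 25% does not yield 150 per group on either reading. The calculation behind the stated size is almost certainly 40% with conventional management versus 25% with PBM.

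On that basis the sample size, the dropout allowance and the 80% power all stand, and the fault lies in the stated effect and arm label. If a 25% relative reduction is what the sponsor means, 150 per group is less than half of the 354 required (150/354 = 42%), and power is about 45%. These figures rest on the article's stated test, α, power and 40% control rate. The step to 25% under PBM is an inference from the reproduced sample size, since the article never states that rate.

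**What to change.** Confirm the two rates against the PASS input. Then, in the Sample Size section and in the abstract's Study Hypothesis:

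- State both rates: transfusion rate 40% with conventional management and 25% with PBM, an absolute reduction of 15 percentage points (37.5% relative).
- Remove the phrase about a reduction by up to 25%. It names a ceiling, whereas a power calculation needs one fixed difference.
- Correct the assumption that assigns 40% to the PBM arm.
- Add that power for a 25% relative reduction (40% to 30%) is about 45% with 150 evaluable per group.

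If the input was 40% versus 25%, the cost is wording only, and 150 and 167 per group stay as they are. If the sponsor instead intends a 25% relative reduction, wording will not suffice: the same method needs 354 per group, or 354 / 0.9 = 393.3, so 394 enrolled per group.

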### Randomization and Blinding

Patients will be randomly assigned in a 1:1 ratio to the patient blood management group and the conventional management group. A randomization table will be prepared using SAS software (SAS Institute, Cary, North Carolina, USA) by an independent statistician and study patients will be assigned using the stratified block randomization method. Stratification will be performed according to the type of cancer, International Federation of Gynecology and Obstetrics stage, and methods of surgery. Due to the nature of the study, blinding is not possible.

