#### Step 1: Anemia Correction in Surgery

Blood tests will be performed between 2 and 6 weeks before surgery and anemia will be corrected according to the test results for each group as follows. The treatment and examination schedule for step 1 is shown in Figure 2.

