##### Patient Blood Management Group

If the hemoglobin level is between 7 g/dL and 12 g/dL in the preoperative blood test, 1000 mg of ferric carboxy-maltose will be administered between 2 and 6 weeks before surgery. During surgery, the need for transfusion will be decided according to the judgment of the attending surgeon and anesthesiologist in case of hemodynamic instability. A blood test will be performed the day after surgery, and if the hemoglobin level is between 7 g/dL and 12 g/dL, 1000 mg of ferric carboxy-maltose will be administered; if the hemoglobin level is 7 g/dL or less, two packs of red blood cells (RBC) will be transfused. The hemoglobin level will be re-evaluated at 3 weeks post-operatively.

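### Randomisation is stratified by FIGO stage, which can only be presumptive at allocation for some patients, while entry haemoglobin, which is known and sets the pre-operative rules, is left to chance

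*Protocol article*

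**What the plan says.** **Strata.** The Randomization and Blinding section of the protocol article allocates 1:1 and states that "study patients will be assigned using the stratified block randomization method". The factors are fixed: "Stratification will be performed according to the type of cancer, International Federation of Gynecology and Obstetrics stage, and methods of surgery". Hb is not among them. The section does not say whether stage means a clinical or imaging stage or a surgical-pathological one, or whether the surgical method is the planned or the performed one.

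**Timing.** Under Step 1, "Blood tests will be performed between 2 and 6 weeks before surgery and anemia will be corrected according to the test results". In the patient blood management arm, "1000 mg of ferric carboxy-maltose will be administered between 2 and 6 weeks before surgery". The time of randomisation is not stated, but the arm must be known by then.

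**Who enters.** The inclusion criteria require histological diagnosis, "including cases diagnosed by imaging without biopsy in the case of ovarian cancer". The Hb criterion is "pre-operative hemoglobin ≥7 g/dL" with no upper limit, so anaemic and non-anaemic patients are both eligible. The Introduction puts anaemia before surgery at 26% to 36%.

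**What Hb decides before surgery.** The iron rule in the patient blood management arm begins "If the hemoglobin level is between 7 g/dL and 12 g/dL in the preoperative blood test". In the conventional arm, Hb of 8–10 g/dL leads to one pack of red cells and 8 g/dL or less to two.

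**The concern.** A stratification factor should be known in the same form for every patient when the arm is assigned, and should predict the primary endpoint. The chosen set falls short on both counts.

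Stage is uncertain at allocation for at least one admitted group. A patient with presumed ovarian cancer and no tissue diagnosis can have only a presumptive stage some weeks before surgery. Balance on the value entered then need not be balance on the stage recorded later.

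Entry Hb is available for everyone, because it is an eligibility criterion. It decides who gets pre-operative iron in one arm and who gets pre-operative red cells in the other. It can therefore be expected to predict transfusion strongly, all the more if transfusions before surgery count, as the Sample Size section implies when it speaks of transfusion before, during and after surgery. At stake are precision and a comparison free of visible imbalance in an important baseline factor.

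**Working it through.** **1. The plan's sample size.** Inputs from the Sample Size section: control rate 40%, two-sided alpha 0.05, power 80%, unpooled Z-test, 10% dropout. The stated reduction reproduces the total only if read as a fall to 25%.

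n = [p1(1−p1) + p2(1−p2)] × (1.960 + 0.842)² / (p1−p2)²
= (0.2400 + 0.1875) × 7.849 / 0.0225 = 149.1, hence 150 per group; 150 / 0.90 = 166.7, hence 167.

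The plan's 150 and 167 are reproduced. The choice of strata does not alter them.

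**2. Chance imbalance in the anaemic share.** Input: 26–36% anaemic (Introduction; midpoint 31%). The calculation assumes that the other strata do not balance Hb indirectly. If Hb differs by cancer type they would do so in part, and the figures would be somewhat smaller.

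SD of the between-arm difference = √[2π(1−π)/n], with n = 150:

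| Anaemic share π | SD (points) | 95% range (points) | P(gap > 10 points) |
|---|---|---|---|
| 26% | 5.1 | ±9.9 | 4.8% |
| 31% | 5.3 | ±10.5 | 6.1% |
| 36% | 5.5 | ±10.9 | 7.1% |

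With all 167 per arm the SD is 4.8–5.3 points and the probability 3.7–5.7%.

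**3. What a gap does to the estimate.** The article gives no transfusion risk by Hb. Two values are assumed for anaemic control patients, 70% and 85%, with the overall rate held at 40% and 31% anaemic. The risk in non-anaemic patients is then

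(0.40 − 0.31×0.70)/0.69 = 26.5%, or (0.40 − 0.31×0.85)/0.69 = 19.8%.

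A 10-point gap shifts the apparent difference by 0.10 × (0.70 − 0.265) = 4.3 points, or 0.10 × (0.85 − 0.198) = 6.5 points, against the 15 points for which the trial is sized. A one-SD gap (5.3 points) shifts it by about 2.3 or 3.5 points.

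**4. Type I error and power.** Simulation with 40,000 trials per setting, 150 per arm, the risks above, and the same relative effect (25/40) in anaemic and non-anaemic patients. The adjusted test is Cochran–Mantel–Haenszel by anaemia status.

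| Anaemic control risk | Anaemic share balanced? | Type I error, unadjusted | Type I error, adjusted | Power, unadjusted | Power, adjusted |
|---|---|---|---|---|---|
| 70% | no | 0.051 | 0.049 | 80.2% | 84.6% |
| 70% | exactly | 0.032 | 0.049 | 81.7% | 84.6% |
| 85% | no | 0.051 | 0.051 | 80.2% | 90.7% |
| 85% | exactly | 0.013 | 0.050 | 84.0% | 90.9% |

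Leaving Hb to chance does not inflate type I error. Balance alone gains about 2–4 points of power. Adjustment gains more, with or without balance. Balance without adjustment makes the unadjusted test conservative (0.032 and 0.013), so a stratum on Hb should be carried into the analysis.

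**5. Cell counts.** The numbers of stage and surgery levels are not given. Assuming 2–4 stage levels and 2–3 surgery levels:

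- Present scheme: 3 × (2–4) × (2–3) = 12–36 cells; 334/12 = 27.8 to 334/36 = 9.3 patients per cell.
- Three Hb levels added: 36–108 cells; 9.3 down to 3.1 per cell.
- Three Hb levels in place of stage: 3 × 3 × (2–3) = 18–27 cells; 18.6 down to 12.4 per cell.

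Replacement keeps the cells within the present range; addition makes them sparse.

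**The case against.** The choice of strata is the investigators' to make, and stage over Hb contradicts nothing. A presumptive stage recorded at allocation is a valid stratum even if revised later: allocation stays random and only balance on final stage weakens. Which stage is entered is operational detail that an article may leave to the full protocol. Adjustment for baseline Hb recovers more than a stratum would, and it belongs to an analysis plan that is not shown.

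Most of that stands, and it rules out several stronger readings:

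- *Stage is unknown in many or most patients.* The text supports this only for ovarian cases entered on imaging alone, and gives no share for them.
- *Pre-operative Hb drives every rule.* It does not. Intra-operative transfusion follows clinical judgment in haemodynamic instability, and the rules after surgery and in steps 2 and 3 use Hb measured at those times.
- *Hb is the strongest determinant of the endpoint.* The article does not rank predictors.
- *Most blocks will be incomplete.* No block size is given. With blocks of 4, for illustration, a cell of 9–14 patients holds two or three full blocks and at most one partial block.
- *The analysis stratum will not match the randomisation stratum.* The article specifies no stratified analysis.

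What the objection does not remove is that the factors are fixed in the text, one is uncertain for an admitted group, and the omitted one is measured in every patient and sets the scheduled pre-operative management in both arms.

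**Conclusion.** The point holds as an improvement in efficiency and chance balance. A reader might infer that the scheme biases the comparison or inflates the false-positive rate. It does neither: simulated type I error is about 0.05, and the planned 150 and 167 per group are unaffected.

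The size is modest: the SD of about 5 points and the 5–7% chance of a gap above 10 points rest on the article's own anaemia range and on 150 per arm. The 2–4 points of unadjusted power, and the 85–91% reached with adjustment for Hb, rest on the assumed 70% or 85% risk in anaemic control patients and a common relative effect. The documents do not settle those risks.

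**What to change.** **If the randomisation table can still be changed:** use the pre-operative Hb category at screening as a stratum in place of FIGO stage, and keep cancer type. Cut-offs at the protocol's own 10 and 12 g/dL give three levels. The 8 g/dL threshold in the conventional arm changes the number of packs, not whether a patient is transfused, so a yes/no endpoint does not need it as a further level. State when randomisation takes place, and define the surgery stratum as the planned approach. Include the Hb category in the primary analysis.

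**If enrolment is under way:** leave the scheme unchanged, since a switch would create two randomisation regimes across 15 institutions. For any stratified analysis use the stage value entered at randomisation, not the post-operative one. Pre-specify baseline Hb as a covariate in the primary analysis; in the simulation this delivers most of the gain.

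**Cost:** before enrolment, a revised table and a short protocol edit; afterwards, an entry in the analysis plan. Neither changes the sample size or any treatment rule. The downside of replacing the stratum is that exact balance on stage is given up; stage can be handled as a covariate.
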